#### Cycle 1: Sampling and Recruitment

This cycle will be implemented during the first semester (fall term) of the third year in the nursing program. An innovative course will be introduced, incorporating GBL strategies and hands-on practice with an AI virtual human platform. Each student will be provided with a personal log-in account to access the system. During the practical sessions, students will work in small groups to engage in guided online simulations. In addition, they will be encouraged to access the platform outside of class time to enhance their empathic communication, emotion recognition, suicide risk assessment, and clinical decision-making skills. Both quantitative and qualitative data will be collected during this phase to inform revisions and improvements for the second cycle of the action research.

#### Cycle 2: Sampling and Recruitment

This cycle will be conducted during the second semester (spring term) of the third year for a new cohort of nursing students. On the basis of the results, feedback, and reflective evaluations gathered from faculty and students during the first cycle, the instructional content and design of the GBL activities and AI virtual human interactions will be refined. The revised intervention will then be implemented as part of a second action research cycle, with the aim of enhancing the overall effectiveness of the innovative teaching approach and achieving the study’s educational objectives.

### Phase 3: Final Evaluation of the Innovative Teaching Intervention

At the conclusion of the 2-semester implementation period, the principal investigator will conduct a comprehensive evaluation of student learning outcomes. This will include analysis of system-generated learning data from the Virti platform, along with the pretest and posttest results from the AEIS administered during both cycles. A comparative analysis of students’ learning outcomes across the 2 implementations will be conducted, integrating both quantitative and qualitative data. The final phase will conclude with the preparation of a comprehensive research report summarizing the findings and implications of the teaching innovation.

Figure 2 presents the combined SPIRIT (Standard Protocol Items: Recommendations for Interventional Trials) 2013 schedule of enrollment, interventions, and assessments for the full 36-week study. Consistent with the SPIRIT 2013 recommendations, the figure maps all key events across 2 action research cycles: cycle 1 (weeks 1-18) and cycle 2 (weeks 19-36). Shaded cells pinpoint the specific weeks in which each activity occurs: enrollment (week 1 and week 19), baseline administration of the AEIS (week 3 and 21), weekly game-based workshops, AI virtual human practice sessions, biweekly reflection logs (even-numbered weeks), and postintervention AEIS assessments (week 18 and week 36). A vertical dashed line at weeks 18-19 delineates the transition between cycles, providing a clear visual alignment of recruitment, intervention delivery, and outcome measurement throughout the study.

**Figure 2 figure2:**
[figure not shown]
Combined SPIRIT (Standard Protocol Items: Recommendations for Interventional Trials) schedule of enrollment, interventions, and assessments for cycle 1 (weeks 1-18) and cycle 2 (weeks 19-36).

### Sample Size and Power Analysis

Using G*Power 3.1 (Heinrich Heine University) for a paired sample 2-tailed *t* test (“Means: difference between two dependent means, matched pairs”), we set α=.05, desired power=.80, and a medium anticipated effect size of Cohen *d*=0.50—consistent with meta-analytic estimates for short educational interventions targeting EI. The calculation yielded a required completer sample of 32 students to detect the pretest-posttest difference with 80% power. Allowing for typical nursing-course attrition of 15% to 20%, we plan to recruit 40 participants per cycle, ensuring that at least 32 remain for posttest analysis.

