**Results:**

Scenario development and expert review were completed in phase 1. Cycle 1 (weeks 1-18) has begun from September 2025, with 37 students enrolled, exceeding the sample size target of 32. Postintervention Adult Emotional Intelligence Scale results will be collected by week 16, followed by cycle 2 with a new cohort. Final integration and analysis will occur after week 36 to evaluate intervention effectiveness.

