Descriptive statistics (means and SDs or medians and IQRs) will be reported for all variables. The normality of pretest-posttest difference scores will be checked with the Shapiro-Wilk test. If the distribution is normal, within-participant changes in AEIS total and subscale scores will be analyzed with paired sample 2-tailed *t* tests; otherwise, the Wilcoxon signed rank test will be used. Effect sizes will be expressed as Cohen *d* with 95% CIs. To compare change trajectories between cycles, an LMM with random intercepts for participants will be fitted, including fixed effects for time (before the intervention vs after the intervention), cycle (1 vs 2), and their interaction (time × cycle). Holm-Bonferroni adjustment will control the family-wise error rate across AEIS subscales. All analyses will follow an intention-to-treat principle (participants with ≥1 posttest record retained); sensitivity checks with complete-case data will evaluate robustness. Statistical significance is set at α=.05 (2-tailed). Analyses will be conducted in SPSS software (version 29.0; IBM Corp) and R (version 4.4.0; R Foundation for Statistical Computing; *lme4* package for LMMs).

To capture students’ experiences and perspectives, we collected qualitative data through structured reflective reports and oral and written feedback after the implementation of the innovative teaching practices. Each student was required to complete a reflective report structured around 5 open-ended questions aligned with the core learning domains of self-awareness, emotional self-awareness, social awareness, empathic communication, and crisis management competence; for example, students described personal insights gained from participating in the card-based educational game, emotional reactions experienced during gameplay, and strategies for recognizing and responding to peers’ emotional cues. They also reflected on their ability to demonstrate empathy in simulated dialogues with AI virtual patients and articulated how these experiences contributed to their confidence in managing psychological crises. Each reflective entry was expected to exceed 100 Chinese characters, thereby encouraging deeper engagement and detailed narrative accounts of their learning processes.

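### The paired t-test calculation described needs 34 completers per cycle, not 32; 32 gives 78% power, and the 37 students enrolled should not be compared with a completer number

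*Protocol article*

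**What the plan says.** The section Sample Size and Power Analysis names the software (G\*Power 3.1) and the routine, "Means: difference between two dependent means, matched pairs", with a two-tailed test. The settings are given as "we set α=.05, desired power=.80" and a "medium anticipated effect size of Cohen *d*=0.50". The result is reported as: "The calculation yielded a required completer sample of 32 students to detect the pretest-posttest difference with 80% power". The same section assumes attrition of 15% to 20% and plans 40 recruits per cycle so that 32 or more are left at posttest.

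The analysis section, Data Collection and Analysis Plan, also sets a two-tailed 5% level, so there is no doubt about sidedness.

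The Results paragraph of the Abstract reports 37 students enrolled in cycle 1 and describes this as "exceeding the sample size target of 32".

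**The concern.** Every input to the calculation is printed, so a reader can repeat it, and the t test named does not return the number reported. This is the only justification of size in the article. The planned 40 equals 32/0.80, so it was evidently built on the lower figure at the upper attrition limit.

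The Abstract then uses 32 in a second way. It compares a count of students enrolled with a count of students expected to finish. That makes cycle 1 look comfortably above target when it is below the planned recruitment of 40. At stake are the accuracy of the stated power and the way cycle 1 is described, both of which may be carried into cycle 2 and the results paper.

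**Working it through.** **Inputs (all from Sample Size and Power Analysis unless noted).** Paired t test, two-tailed; α = 0.05; target power 0.80; d = 0.50, taken as the standardised mean of the paired differences; attrition 15% to 20%; 40 recruits per cycle. Cycle 1 enrolment of 37 is from the Abstract, Results.

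**1. Reproducing the stated 32.** Normal approximation for a paired difference:

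n = ((z₀.₉₇₅ + z₀.₈₀)/d)² = (1.960 + 0.842)²/0.25 = 31.4, rounded up to 32.

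Power at 32 by the same approximation is Φ(0.5√32 − 1.960) = Φ(0.868) = 0.807. The stated figure is therefore reproduced exactly, but by a z calculation.

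**2. The t test that is named.** Exact power is the probability that a noncentral t variable with n − 1 degrees of freedom and noncentrality 0.5√n falls outside ± the 97.5% point of t with n − 1 degrees of freedom.

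| Completers | Two-tailed power at d = 0.50 |
|---|---|
| 29 | 0.739 |
| 30 | 0.754 |
| 31 | 0.768 |
| 32 | 0.782 |
| 33 | 0.795 |
| 34 | 0.808 |

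The smallest n with power of at least 0.80 is 34. With 32 completers, 80% power is reached at d = 0.511.

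**3. Could sidedness explain 32?** No. With a one-tailed t test, 27 completers already give power 0.812.

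**4. Attrition with 40 recruits.**
- 15%: 40 × 0.85 = 34 completers, power 0.808.
- 20%: 40 × 0.80 = 32 completers, power 0.782.
- To keep 34: 34/0.85 = 40 recruits at 15%; 34/0.80 = 42.5, so 43, at 20%.

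**5. Cycle 1 with 37 enrolled.**
- 15%: 37 × 0.85 = 31.45, about 31 completers, power 0.768.
- 20%: 37 × 0.80 = 29.6, so 29 completers if rounded down, power 0.739 (0.754 if 30).
- To end with 32 completers, cycle 1 can lose 5 of 37 (13.5%). To end with 34, it can lose 3 of 37 (8.1%). Both lie below the protocol's assumed 15% to 20%.

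**The case against.** The strongest reply is that the gap does not matter in practice. It is 2 students, or 1.8 points of power, and it moves the detectable effect from 0.50 to 0.511. The assumed effect is a rounded medium value and is far less certain than that. The figure 32 also follows from a standard approximation. This stands as an argument about size. It does not make the sentence correct, because the article attributes 32 to a t-test calculation and mentions no approximation.

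A reader might infer that the recruitment plan fails. The documents do not support this. The article promises only that 32 or more remain, and 40 × 0.80 = 32, so the plan is consistent with its own figure. Against the correct 34, 40 recruits are still enough at 15% attrition. They fall short only towards the 20% end.

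A reader might also infer that the study as a whole is underpowered. That does not follow. The 78% applies to a paired t test within one cycle. There are two cycles, and the analysis section treats the mixed model as primary and the paired tests as ancillary. If both cycles contributed to one time effect, and that effect were the same in each, 64 completers would give about 98% power at d = 0.50. The single-cycle figure remains relevant because the Methods overview says each cycle is evaluated by its own pretest-posttest comparison, and the sample size section plans recruitment per cycle.

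**Conclusion.** The point holds as a minor numerical error. The calculation described needs 34 completers per cycle; 32 is the normal-approximation answer and gives 78.2% power. With 40 recruits and the protocol's own attrition range, power is 78% to 81%, close to the intended 80%, so the design is not in question.

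The wording in the Abstract has the larger numerical consequence. Cycle 1 enrolled 3 fewer than planned, and at the assumed attrition about 29 to 31 completers and 74% to 77% power are expected. Calling this an excess over target is not a like-for-like comparison.

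These figures assume that d = 0.50 refers to the paired differences, as the named routine implies, that differences are roughly normal, and that attrition in cycle 1 is 15% to 20%. If fewer students drop out, the cycle 1 shortfall shrinks or disappears: with no more than 3 losses, 34 would complete.

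**What to change.** In Sample Size and Power Analysis, replace the result and the recruitment sentence with text such as: *A two-tailed paired t test at α = .05 needs 34 completers per cycle for 80% power at d = 0.50. Recruiting 40 per cycle, with 15% to 20% attrition, leaves 32 to 34 completers and gives 78% to 81% power for a single-cycle comparison.* If the authors prefer to keep 32, they should say that it is a normal approximation and that the t-test power at 32 is 78%.

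In the Abstract, Results, drop the comparison of 37 with 32. Say instead that 37 of the planned 40 were enrolled in cycle 1 and that, at the assumed attrition, about 29 to 31 completers are expected, with power of about 74% to 77%. Once the cycle 1 posttest is complete, the actual number of completers can replace the projection.

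The cost is a text edit in two places. No change to enrolment, data collection or analysis is needed; stated power at 32 completers falls by about 2 points.

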#### Data Collection and Analysis Plan

This study adopts a single-group pretest-posttest design implemented across 2 instructional cycles (first and second semesters). Quantitative data will be gathered with the AEIS—a validated 26-item instrument covering 4 subscales: emotion awareness (items 1-7), emotional expression (items 8-12), emotion regulation (items 13-17), and emotional use (items 18-26). Each item is scored on a 4-point Likert scale (ranging from 0=strongly disagree to 3=strongly agree); higher scores denote greater EI [22]. Permission to use the AEIS has been obtained from the original author. The scale will be administered in week 3 (pretest evaluation) and week 16 (posttest evaluation) of each semester. Qualitative data will consist of students’ reflective reports—collected throughout both cycles—and classroom observations conducted in week 17 to document behavioral engagement during gameplay and AI-patient interactions.

At the item level, AEIS subscale scores will be prorated when no more than 1 item per subscale is missing; otherwise, the subscale will be set to missing. At the record level, patterns of missingness will be inspected with the Little MCAR test [23]. As linear mixed effects models (LMMs) provide unbiased estimates under a missing-at-random assumption, incomplete cases will be retained in the primary analyses. For ancillary paired sample 2-tailed *t* tests or Wilcoxon signed-rank tests, missing posttest values will be multiply imputed (20 imputations using predictive mean matching); the imputed results will be pooled following the rules formulated by Rubin [23] and compared with complete-case outputs as a sensitivity check.

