### Ethical Considerations

This teaching project has been approved for funding (see Multimedia Appendix 3) and is under review by the central regional research ethics committee of China Medical University, Taichung, Taiwan review board (T-AU-36938) to ensure adherence to ethical standards in research involving human participants. All data collected in this study will be handled in accordance with institutional review board ethical guidelines to ensure participant privacy and data security. Participants will be assigned unique ID codes, and no personally identifiable information will be linked to the analysis. Digital data, including survey responses, reflection journals, and system use logs, will be stored on encrypted and password-protected institutional servers accessible only to the principal investigator and authorized research team members. All documents will be kept in locked cabinets in secure university offices. All data will be retained for a maximum of 5 years and then permanently destroyed in accordance with institutional policies. Results will be reported in aggregate form to prevent individual identification. Participation in this study is voluntary, and informed consent will be obtained from all participants before data collection. Participants may withdraw at any time without penalty or impact on their academic standing.

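### Course leavers are planned as lost posttests, and the set labelled intention-to-treat is in effect a posttest-completer set that conflicts with the mixed-model plan

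*Protocol article*

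**What the plan says.** Under Sample Size and Power Analysis the protocol article derives 32 completers per cycle and inflates that number: "Allowing for typical nursing-course attrition of 15% to 20%, we plan to recruit 40 participants per cycle, ensuring that at least 32 remain for posttest". The loss rate applied to the posttest is a course attrition rate.

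The Data Collection and Analysis Plan makes two statements about students without a posttest. On missing data, it says of the linear mixed model that "incomplete cases will be retained in the primary analyses", on a missing-at-random assumption. Missing posttests are multiply imputed only for the ancillary paired t or Wilcoxon tests, and those results are compared with complete cases. Later in the same section, "All analyses will follow an intention-to-treat principle", which a parenthesis then defines as keeping participants who have one or more posttest records.

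Ethical Considerations has one sentence on withdrawal: "Participants may withdraw at any time without penalty or impact on their academic standing". It does not say whether leaving the course and withdrawing from data collection are the same event.

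**The concern.** Leaving a course and refusing to complete a questionnaire are different events. The AEIS is a 26-item self-report form and is not an output of the simulation platform. Sampling and Recruitment asks participants to be willing to complete both AEIS forms, and it excludes suspended students or those on leave only as of recruitment. Nothing stated makes a student who leaves later ineligible for the posttest. Yet the sample size text counts that student as having none, and the article describes no attempt to obtain one.

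Students who leave may be those for whom the teaching model worked least. If they are unobserved, the reported change describes those who stayed, while the label intention-to-treat suggests the whole cohort. There is no control arm in which similar dropout might be seen. Cycle 1 results also feed the revision of the intervention for cycle 2, so the same gap carries into that decision.

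**Working it through.** **1. The plan's own figure.** Inputs from Sample Size and Power Analysis: "we set α=.05, desired power=.80, and a medium anticipated effect size of Cohen *d*=0.50", "for a paired sample 2-tailed *t* test".

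- Normal approximation: n = ((1.960 + 0.842)/0.50)² = 31.4, rounded up to 32. This matches "The calculation yielded a required completer sample of 32 students to detect the pretest-posttest difference with 80% power".
- The noncentral t distribution gives 34 (power 0.808), with power 0.782 at 32. The difference is small and does not affect this point.
- Inflation: 32/(1 − 0.20) = 40 and 32/(1 − 0.15) = 37.6, rounded up to 38. The 40 is correct for 20% loss.

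The attrition arithmetic is therefore sound. The issue is what the attrition stands for.

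**2. Posttests unobserved.** 40 × 0.15 = 6 and 40 × 0.20 = 8 per cycle. That leaves 34 or 32 observed, or 85% to 80%.

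**3. Who is in the analysis set.** Each cycle has one AEIS posttest, and cycle 2 recruits a new cohort, so a student can have at most one posttest record.

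- Under the intention-to-treat definition, a student with a pretest and no posttest is out.
- Under the missing-data paragraph, the same student is kept in the primary mixed model, and the missing posttest is imputed for the ancillary tests.

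Both rules cannot hold for that student. The first gives a completer analysis. The second relies on missing at random: the model adjusts only for the part of a leaver's difference that the observed data predict, here mainly the pretest score. The planned Little test addresses missing completely at random, so it cannot confirm missing at random.

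**4. Possible size of the bias.** With p the proportion leaving, and effects in units of the stayers' SD of change:

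d(all) = (1 − p) × d(stayers) + p × d(leavers), with d(stayers) = 0.50 as planned.

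| Assumed d(leavers) | p = 0.15 | p = 0.20 |
|---|---|---|
| 0 | 0.85 × 0.50 = 0.425 | 0.80 × 0.50 = 0.40 |
| 0.25 | 0.425 + 0.0375 = 0.4625 | 0.40 + 0.05 = 0.45 |
| 0.50 | 0.50 | 0.50 |

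In the first row a completer estimate of 0.50 is too high by 0.50/0.425 = 1.18 to 0.50/0.40 = 1.25, that is, by 18% to 25%. In the last row there is no bias. The documents give no value for d(leavers).

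**5. Effect on precision (noncentral t, d=0.50).** Power is 0.782 with 32 posttests, 0.808 with 34 and 0.869 with all 40. If 5% or 10% were still lost (assumed), 38 or 36 posttests give 0.851 or 0.831.

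For cycle 1 the abstract reports "with 37 students enrolled, exceeding the sample size target of 32". That 32 is the completer requirement; the recruitment plan was 40. At the plan's own attrition, 37 × 0.85 = 31.45 and 37 × 0.80 = 29.6, so about 30 to 31 posttests and power of about 0.75 to 0.77. All 37 would give 0.84.

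**The case against.** The strongest reply is that the 15% to 20% is a recruitment allowance and not a data-collection rule. Budgeting for loss does not mean refusing a posttest from a student who leaves, and no sentence says collection stops. This stands: the plan cannot be said to forbid these posttests. What it does is count them as lost while describing no attempt to obtain them.

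A second reply is that levels of withdrawal and follow-up of leavers belong in the full protocol and consent form, which are not shown. This also stands for the missing procedure, so the point does not rest on it. It rests on two things the article states: course attrition used as posttest loss, and an intention-to-treat set defined by having a posttest.

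Two stronger readings are tempting and are not supported.

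- A reader might infer that the intention-to-treat estimate rests on imputed data. It does not. The primary mixed model uses no imputation, imputation is confined to the ancillary paired tests and checked against complete cases, and 80% to 85% of posttests would be observed even at the planned attrition.
- A reader might infer that a student who merely skips the game or simulation sessions is planned as lost. The sample size text speaks only of course attrition. A student who stays enrolled still falls under the scheduled AEIS administration.

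Finally, it is fair to say that zero change in leavers is hypothetical and that reaching them is assumed. Survey responses are listed among the stored digital data, but the article does not say the AEIS is completed online or that leavers can be contacted.

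**Conclusion.** The point holds in limited form. The article plans course attrition as loss of the AEIS posttest (6 to 8 of 40 per cycle). Its intention-to-treat set is a posttest-completer set, which contradicts the retention of incomplete cases in the same section. For leavers, the estimate depends either on excluding them or on an untestable missing-at-random assumption.

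The consequence ranges from no bias, if leavers change as stayers do, to a whole-cohort effect of about 0.40 to 0.425 against 0.50 in stayers, if leavers do not change at all. Without observed posttests from leavers, the data cannot tell these cases apart. The range rests on the protocol's own attrition rate and planned effect size; the leavers' change is assumed. The sample size arithmetic is not in error. This is an inexpensive improvement that should be made, together with correction of an inconsistent definition.

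**What to change.** 1. In the Data Collection and Analysis Plan and in Ethical Considerations, separate leaving the course from withdrawing consent to data collection. Only the second ends AEIS collection.
2. Offer the AEIS, for example by online link, at the scheduled posttest week to every student with a pretest who has not withdrawn that consent, whatever their course status. Record the reason for leaving. The article gives week 16 of each semester in one place and weeks 18 and 36 in another; settle that first.
3. Analyse these posttests as observed.
4. Replace the intention-to-treat definition with all students who have a pretest, consistent with the mixed model. Keep the complete-case analysis as the sensitivity check already planned.

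The cost is information-sheet wording or an ethics amendment, which may be practical only for cycle 2 because cycle 1 has begun, and contact with about 6 to 8 students per cycle. Response among leavers will be partial, and their forms will be completed outside class, so the setting differs from that of the other students. Whether leavers can be reached should be checked before the plan relies on it.
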